### Eligibility, exclusion, and withdrawal criteria

The eligibility criteria are as follows: (1) age between 18 and 75 years, (2) clinical findings of CHF for at least 3 months prior to screening, (3) CHF caused by coronary heart disease and hypertension, which is diagnosed according to the Chinese guidelines published in 2014 [10] for the diagnosis and treatment of heart failure, (4) in a clinically stable condition with a New York Heart Association (NYHA) functional class of II to III and an optimal medical treatment with a fixed dosage for at least 2 weeks, (5) a documented left ventricular ejection fraction (LVEF) ≤ 40% and a serum *N*-terminal pro-B-type natriuretic peptide (NT-proBNP) level ≥ 450 pg/ml, (6) CHF of *Qi* deficiency and blood stasis syndrome based on TCM syndrome differentiation, and (7) provision of written informed consent.

The exclusion criteria are stated as below: (1) CHF accompanied by severe valvular heart disease, congenital heart disease, pericardial disease, cardiomyopathy, unstable angina, acute myocardial infarction (in the recent 4 weeks), cardiogenic shock, acute myocarditis, infective endocarditis, or uncontrolled severe cardiac arrhythmia with hemodynamic changes; (2) pulmonary heart disease, pulmonary hypertension caused by acute or chronic pulmonary embolism or cerebral apoplexy in the last 6 months; (3) severe hepatic inadequacy with alanine aminotransferase or alkaline phosphatase levels more than twice the upper normal limit, renal inadequacy with a serum creatinine level > 3 mg/dl (>265 μmol/L), severe electrolyte imbalance, severe hematologic disease, malignant tumor, diabetes mellitus with severe complications, or severe endocrine diseases such as hyperthyroidism and hypothyroidism; (4) acute infection confirmed by any one of the following three indicators: (a) fever, (b) a white blood cell count > 10 × 10^9^/L and a percentage of neutrophils > 75%, (c) shadow on chest X-ray, (d) uncontrolled blood pressure or fibrosis in other organs, (e) CHF of *yin* deficiency according to TCM syndrome differentiation, (f) pregnancy or breastfeeding, (g) psychiatric or infectious disease, and (h) patients who have participated in other clinical trials in the past 2 months.

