### Secondary outcomes

The secondary outcomes of this study are as follows:Composite cardiac events (CCEs): CCEs are defined as death, readmission for heart failure and other cardiovascular events such as acute coronary syndrome, serious cardiac arrhythmias, cardiac shock, etc. We will carry out continuous monitoring of CCEs and evaluate the links between CCEs and test drugs. The assessments of safety and tolerability will be based on spontaneous reports of adverse events, vital signs and laboratory testsNYHA functional classification: based on the NYHA functional classification, the investigators will grade the severity of functional limitation and patient estimates of how far they are able to walk before they become breathless6-minute walking distance (6MWD): participants will be instructed to walk as far as possible over a period of 6 min. This test is scored in rounded meters walked in 6 minLVEF: left ventricular ejection will be obtained from all participants by an experienced echocardiographic technician in each local participating center, who is blind to the allocation of the patientsPatient quality of life: The Chronic Heart Failure Quality of Life Scale of Integrated Chinese and Western Medicine [13] will be used to evaluate all patients. An additional file shows this in more detail (see Additional file 2)TCM syndrome integral scale: TCM symptoms of all patients will be assessed through TCM syndrome integral scale

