## Data collection and management

A CRF will be used for each participant to collect relevant data. The participants will be evaluated every 4 weeks during the study. Data on CCEs, NYHA functional classification, 6MWD, patient quality of life and the TCM syndrome integral scale will be collected at each visit (week 0 ± 3 days, week 4 ± 3 days, week 8 ± 3 days, and week 12 ± 3 days). The NT-proBNP and LVEF will be measured only at the first and the last visit (week 0 ± 3 days and week 12 ± 3 days). The Standard Protocol Items: Recommendations for Interventional Trials (SPIRIT) flowchart of the trial can be found in Fig. 2.

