## Statistical analysis

### Sample size calculation

The sample size was calculated based on the expected reduction in serum NT-proBNP levels during the study. Previous studies showed that the prognosis of patients with an NT-proBNP level decrease by at least 30% from baseline through treatment is better than in those not treated [14, 15]. Therefore, according to another previous study on treating CHF with Chinese herbal medicine [4], the proportion of patients demonstrating a more than 30% decrease in NT-proBNP level in the placebo group is 31.98% (*P*
_1_ = 0.3198). According to previous clinical results, the investigators assumed that the proportion of patients demonstrating a more than 30% decrease in NT-proBNP level in the QSG group would be 53% (*P*
_2_ = 0.53). Given a type-I error rate of *α* = 0.05 and a type-II error rate of *β* = 0.2, and considering a dropout rate of approximately 20% among randomized patients, the investigators plan to include a total of 200 subjects. The relevant formulas are shown as follows:$$ \mathrm{n}={\left({\mathrm{Z}}_{1-\alpha /2}+{\mathrm{Z}}_{1-\beta}\right)}^2\times \left[{\mathrm{P}}_1\left(1-{\mathrm{P}}_1\right)+{\mathrm{P}}_2\left(1-{\mathrm{P}}_2\right)\right]/{\delta}_2 $$
$$ \mathrm{N}=2{\mathrm{n}}^{\ast}\left(1+20\%\right) $$

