### Data analysis

Data entry and management will be completed by an independent data administrator to ensure data accuracy. A professional statistician will perform the data analysis for the results. We will use the intent-to-treat principle to analyze the efficacy and safety of QSG. For continuous variables, the independent two-sample Student’s *t* test will be used for comparisons between the two study groups, and the paired test will be used for intra-group comparisons. The *χ*2 test will be used for categorical variables. When continuous data distribution is not normal, the Wilcoxon test will be used. *P* < 0.05 is considered to be statistically significant, and all tests are two-tailed.

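### The only test named for categorical data ignores the ordering of NYHA class; under a uniform shift this costs roughly 9 to 18 points of power on that secondary outcome

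*Protocol article*

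**What the plan says.** The Data analysis section assigns tests by type of variable. Continuous variables get a t test. For the rank test the rule is "When continuous data distribution is not normal, the Wilcoxon test will be used". For everything categorical, the χ² "test will be used for categorical variables". The threshold of P < 0.05 "is considered to be statistically significant, and all tests are two-tailed". The section names no ordinal or trend test and does not mention NYHA class by name.

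NYHA class is listed under Secondary outcomes, where "the investigators will grade the severity of functional limitation". It is therefore a graded scale. Entry is limited to a "New York Heart Association (NYHA) functional class of II to III", so there are two baseline levels. The Data collection and management section adds: "Data on CCEs, NYHA functional classification, 6MWD, patient quality of life and the TCM syndrome integral scale will be collected at each visit". The visits are weeks 0, 4, 8 and 12, so the baseline class is on record for every patient. Randomization is stratified by study site.

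**The concern.** A Pearson χ² test on a 2 × 4 table gives the same P value however the four classes are relabelled. It looks for any difference between two distributions and spends up to 3 degrees of freedom on it. If treatment moves patients broadly toward better classes, most of the signal lies in one direction, and a 1-df test that respects the order finds it more often with the same data.

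The trial is sized on NT-proBNP alone, so nothing in the sample size protects the power for NYHA class. The protocol does not leave the test open: it names one, and for an outcome analysed in its four classes it is the less efficient one against the effect most likely to be of interest.

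**Working it through.** **The plan's own figure.** The sample size formula with P1 = 0.3198, P2 = 0.53, two-sided α = 0.05 and β = 0.2 gives n = 82.9, or 83 per arm, and 2 × 83 × 1.2 = 199.2, or 200. The stated total reproduces. It concerns NT-proBNP only; no effect size or power is stated for NYHA class.

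**Inputs for NYHA.**
- Patients per arm: 200 / 2 × (1 − 0.20) = 80, from the stated total and dropout rate.
- α = 0.05, two-sided (Data analysis).
- Placebo split over classes at week 12: not in the document. Assumed 10/50/35/5% over I to IV (four occupied) or 5/55/40% (three occupied).
- Effect: not in the document. Assumed common odds ratio (OR) of 2.0 or 2.5 toward better class.

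**Step 1: loss from degrees of freedom alone.** A noncentrality of λ = 7.849 gives a 1-df test 80% power. If the ordered test captures the whole shift, the same λ gives 71% on 2 df (three classes) and 64% on 3 df (four classes), a loss of 9 and 16 points. Restoring 80% would need about 23% or 39% more patients.

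**Step 2: one setting by hand.** For cumulative placebo proportion C, the active arm has OR·o / (1 + OR·o), where o = C / (1 − C). With four classes and OR 2.0:
- Placebo C = 0.10, 0.60, 0.95; odds 0.1111, 1.5, 19; doubled 0.2222, 3, 38.
- Active C = 0.1818, 0.75, 0.9744, so the classes are 18.2/56.8/22.4/2.6%.
- Mean shift = 0.0818 + 0.15 + 0.0244 = 0.26 class.
- λ = n Σ (p − q)² / (p + q) = 80 × (0.0237 + 0.0044 + 0.0275 + 0.0079) ≈ 5.1, which on 3 df is about 45% power.

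**Step 3: simulation.** Pearson χ² against the unstratified Wilcoxon test with tie correction, 80 per arm; ranges are over repeat runs.

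| Occupied classes | OR | χ² | Wilcoxon | Loss (points) |
|---|---|---|---|---|
| Four | 2.0 | 44% | 61–62% | 17–18 |
| Four | 2.5 | 69–71% | 84–85% | 14–16 |
| Three | 2.0 | 47–48% | 58% | 10–11 |
| Three | 2.5 | 71–72% | 81% | 9–10 |

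Under no effect, both tests rejected in about 4 to 5% of trials.

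**Step 4: where the ranking reverses.** Take placebo 10/50/35/5 against 25/35/35/5, so that the only change is from class II to class I. Then λ = 80 × (0.15²/0.35 + 0.15²/0.85) = 7.3. The χ² test has about 61–63% power and the Wilcoxon test about 18–19%.

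**Step 5: baseline class, kept separate.** In three assumed baseline-to-week-12 patterns (83 per arm, OR 2.0, half the patients in each entry class), stratifying the Wilcoxon test by entry class raised its power from 52% to 61%, from 34% to 53%, and from 62% to 66%. These patterns are invented, so the figures show only that the recorded baseline class can add power. They are not part of the 9 to 18 points. The effect of site was not modelled.

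**The case against.** The strongest reply is that the article never assigns a test to NYHA class. It gives one generic paragraph and does not say whether the outcome is class at week 12, change in class, or improved versus not improved. If it were improvement by at least one class from baseline, χ² would be a conventional 1-df test that already uses baseline. This stands as a limit: the point applies to NYHA analysed in its four classes. No binary definition appears in the article, however, and the rank test is expressly tied to continuous data.

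Three stronger readings are tempting, and the documents do not support them.

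- *The χ² test could miss a consistent one-class improvement.* It would not. Moving every placebo patient up one class turns 10/50/35/5 into 60/35/5/0, and λ = 80 × (0.50²/0.70 + 0.15²/0.85 + 0.30²/0.40 + 0.05²/0.05) = 52.7. Power is essentially 100% with either test. The loss concerns modest shifts, about 0.26 class at OR 2.0 with four classes.
- *The analysis cannot tell improvement from worsening.* The P value has no direction, but the class proportions by arm do. All tests are two-tailed, so a Wilcoxon P value also needs an estimate beside it. The fair remainder is that a significant omnibus result may reflect a mixed pattern.
- *Leaving out baseline class and site is itself a defect.* Covariates and strata are commonly settled in the full protocol or analysis plan, which are not shown. They belong in the remedy, not in the charge.

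**Conclusion.** The point holds as one of efficiency on a secondary outcome. As written, an ordered scale would go to an unordered test. Under a uniform shift with OR 2.0 to 2.5 and 80 per arm, that gives up roughly 9 to 18 points of power: toward the low end if three classes are occupied, and 14 to 18 if four are. The range rests on assumed class distributions and on proportional odds, since the document supplies neither a distribution nor an effect. A non-uniform shift can reverse the ranking, as Step 4 shows.

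A reader might infer that the test is invalid or that the trial's main result is at risk. Neither follows: type I error is held, the primary outcome is a binary responder rate for which χ² is suitable, and N = 200 is unaffected.

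**What to change.** Add one sentence to the Data analysis section: week-12 NYHA class will be compared between arms by an ordinal method that uses baseline class and site. Two suitable forms are:

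- a Wilcoxon (CMH row-mean-score) test stratified by site and baseline class; or
- a proportional-odds model with arm, site and baseline class, reporting the common odds ratio with its 95% CI.

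Reserve χ² for binary items.

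This needs no new data or visits, because class is already recorded at every visit. The article's trial status section says recruitment had not begun, so at that date the wording could be settled before any outcome was seen. The price is some loss of sensitivity to non-monotone or localised patterns and, if the model is chosen, reliance on the proportional-odds assumption. Showing class proportions by arm beside the test would let a reader see such patterns.

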## Randomization

An independent statistician who is unaware of the design and purpose of the study will generate a randomization table by using Statistical Analysis System (SAS, version 9.4). The 200 patients will be randomly allocated in a 1:1 ratio to either the QSG treatment group or the placebo group. The randomization will be stratified by study site. According to the design of the random program, the researcher will open one random envelope and obtain a randomization number for a patient on the day of inclusion. Both investigators and participants will be blind to the allocations.

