### Primary outcome

The primary outcome is the proportion of patients in the QSG group, compared with the placebo group, demonstrating a more than 30% decrease in NT-proBNP level during 12 weeks of treatment.

On the day of inclusion, serum NT-proBNP will be taken as the baseline level of participants who will be enrolled and randomized for this trial before taking the QSG or placebo.

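### Paired before-after tests within each arm are planned under the same P < 0.05 rule as the randomised comparison, although a within-arm change is not a treatment effect

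*Protocol article*

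**What the plan says.** The Data analysis section of the protocol article says that efficacy and safety will be analysed by intention to treat. For continuous variables it names a two-sample t test between the groups and adds that "the paired test will be used for intra-group comparisons". Categorical variables get a chi-squared test, and non-normal continuous data a Wilcoxon test. The section closes with one threshold: "P* < 0.05 is considered to be statistically significant, and all tests are two-tailed". It does not separate the primary from the secondary outcomes, or tests between arms from tests within an arm.

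The primary outcome is defined as a comparison between groups: "The primary outcome is the proportion of patients in the QSG group, compared with the placebo group, demonstrating a more than 30% decrease" in NT-proBNP. The Secondary outcomes section lists six: composite cardiac events, NYHA class, 6-minute walking distance, LVEF, quality of life and the TCM syndrome scale. Under Data collection and management, "The participants will be evaluated every 4 weeks during the study". NT-proBNP and LVEF are the exceptions, measured only at weeks 0 and 12.

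**The concern.** The within-arm tests are a stated method, and they answer a different question from the one the trial was randomised to answer. A paired test asks whether the mean in one arm moved from baseline. It can move because of background heart failure treatment, closer follow-up, expectation, or regression to the mean in patients selected for poor values. Entry requires LVEF of at most 40% and NT-proBNP of at least 450 pg/ml, and background treatment need have been at a fixed dose for only two weeks. Some movement without any drug effect is therefore plausible, although the article gives no figure for it.

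If a paired result is called significant by the same rule as a between-arm result, the two can be read as equal evidence. The usual error is to note a significant change in the QSG arm and none in the placebo arm and to treat that contrast as an effect. It is not a test of the difference between arms. A milder version applies to the six secondary outcomes: with one threshold and no label, an isolated P < 0.05 among them carries less weight than it appears to.

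**Working it through.** **Inputs from the protocol article**
- Threshold 0.05, two-sided (Data analysis).
- One primary outcome, compared between groups (Primary outcome).
- Six secondary outcomes (Secondary outcomes).
- Allocation: "The 200 patients will be randomly allocated in a 1:1 ratio to either the QSG treatment group or the placebo group", so 100 per arm. With the planned dropout of about 20%, 100 × 0.8 = 80 per arm.
- Sample size: "Given a type-I error rate of *α* = 0.05 and a type-II error rate of *β* = 0.2", with responder proportions of 0.3198 (placebo) and 0.53 (QSG).

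**Assumptions, not in the article**
- The size of a non-drug change within an arm: d = mean change divided by the SD of the change, taken as 0.1 to 0.5.
- The correlation between secondary outcomes: 0 to 0.7.

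**Step 1. The plan's own figure.** The divisor in the article's formula is read as the squared difference.

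n = (1.960 + 0.842)² × [0.3198 × 0.6802 + 0.53 × 0.47] / (0.53 − 0.3198)² = 82.9 per arm.

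N = 2 × 83 × 1.2 = 199.2, which agrees with 200. The trial is therefore sized on one between-group test at two-sided 0.05. The type I error of that test is 5%, whatever is done with the other tests.

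**Step 2. How often a within-arm paired test is significant when QSG has no effect.** By normal approximation:

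P(significant) = Φ(d√n − 1.96) + Φ(−d√n − 1.96)

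For d = 0.2 and n = 100, d√n = 2.0, and Φ(0.04) + Φ(−3.96) = 0.516.

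| Assumed non-drug change d | n = 100 per arm | n = 80 per arm |
|---|---|---|
| 0.1 | 17% | 15% |
| 0.2 | 52% | 43% |
| 0.3 | 85% | 77% |
| 0.5 | 99.9% | 99.4% |

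**Step 3. Significant in QSG but not in placebo.** If both arms change by the same amount, the arms are independent and this pattern has probability p(1 − p) for each outcome. With n = 100:
- d = 0.1: 0.170 × 0.830 = 14%
- d = 0.2: 0.516 × 0.484 = 25%
- d = 0.3: 0.851 × 0.149 = 13%

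The true difference between arms is zero in all three cases.

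**Step 4. Six secondary outcomes, one between-arm test each.** If independent, the chance of at least one false P < 0.05 is 1 − 0.95⁶ = 26.5%. Simulation of six equally correlated two-sided tests (200,000 replicates) gives 24.2%, 20.5% and 16.3% at correlations of 0.3, 0.5 and 0.7.

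**The case against.** The strongest reply is that the article already has the right structure. It names one primary outcome, compares it between groups, measures it at baseline and week 12, and sizes the trial on it. The primary and secondary labels imply which result is confirmatory, and the threshold sentence may be no more than a general definition. Unadjusted secondary outcomes are common, and any adjustment is usually left to an analysis plan, which is not shown here. All of this stands, so the lack of a multiplicity scheme is not the point being made.

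Some stronger readings are tempting, and the documents do not support them.
- **Testing at every visit.** A reader might infer from the visit schedule that each outcome is tested at weeks 4, 8 and 12. Four outcomes at three visits plus LVEF and cardiac events gives 14 tests and 1 − 0.95¹⁴ = 51%. Counting cardiac events at each visit gives 16 tests and 56%. The article gives a collection schedule and does not say that each visit will be tested. Independence is also implausible for repeated measurements in the same patients: for 16 tests at correlations of 0.5 to 0.7 the figure is about 38% to 26%.
- **The placebo responder rate as proof of a within-arm shift.** The article assumes that the proportion with a fall of more than 30% "in NT-proBNP level in the placebo group is 31.98"%. That is a responder proportion from an earlier study. Other patients may rise, and no mean change is given, so it does not show that a paired test on a continuous outcome would be significant.
- **An intention to claim efficacy from these tests.** No section says that secondary or within-arm P values will be presented as proof of efficacy.

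None of this removes the within-arm clause. It is written into the plan as a test and falls under the same threshold, and an analysis plan that follows the article would inherit it.

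**Conclusion.** The point holds for the within-arm tests, and in a narrow form for the labelling of the secondary outcomes. The primary analysis is sound in this respect and keeps its 5% error.

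The size of the within-arm problem depends on the non-drug change, which the article does not give. At 0.1 SD a paired test misleads occasionally. At 0.2 to 0.3 SD it does so in about half to most trials with no drug effect (43% to 77% if only 80 per arm remain). For the secondaries, about 16% to 26% is a reasonable range for one test each. That is enough to call for reading them as supportive, and it is not a defect in the design.

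**What to change.** In Data analysis:
- Remove the paired tests as inferential tests. Give within-arm changes descriptively, as mean change with its spread and without P values.
- State that every efficacy statement rests on the between-arm comparison, and that the primary outcome is the one confirmatory test at two-sided 0.05.
- Name week 12, the end of treatment, as the main time point for the secondary outcomes. Report them as between-arm estimates with 95% confidence intervals, labelled supportive.

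This changes wording only. The confirmatory test and its alpha stay as they are, so 200 patients remains the target. The cost is that fewer results can be called significant. The Trial status section says that no patients had yet been recruited, so at that stage the change could be made before any data exist.

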## Discussion

CHF is a major worldwide health problem. Despite the medical and technological advances in treating heart failure, the mortality, morbidity and treatment costs of CHF remain high or are increasing [2]. Myocardial fibrosis plays an important role in the development of heart failure [16]. The renin-angiotensin-aldosterone system (RAAS), especially angiotensin II and aldosterone, play a key role in myocardial fibrosis [17]. Although significant progress has been made in the treatment of heart failure by ACEIs, ARBs, and AAs, recent studies have found substantial limitations in these drugs [18–20]. With its much lower cost and a good effect on CHF, TCM has been widely used in the treatment of CHF in China.

QSG is a TCM formula that has long been used to treat CHF and has good efficacy in clinical practice. Our previous study has also shown that QSG exerted cardio-protective effects and prevented left ventricular remodeling in AMI animal models [21]. Last but not least, QSG was found to have multiple targets associated with the inhibition of RAAS, thus producing cardio-protective therapeutic effects [7].

However, relevant evidence from clinical trials to show its efficacy is still scarce. The purpose of this study is to evaluate the efficacy and safety of QSG in CHF. This trial will provide high-quality evidence on the efficacy and safety of QSG in the treatment of CHF, thus providing reference for the clinical application of QSG.

